### Empirical bioethics study

In parallel with the main study, an empirical bioethics study will be carried out (Borry et al., 2005; Dunn et al., 2012). Drawing from a systematic review exploring the nature of conflicts within dyads from an ethical standpoint (Cincidda et al., ongoing work), namely, what we refer to as “moral conflict”, conflict between patient and caregiver may arise when the latter is involved in the patient's care path (Levine and Zuckerman, 1999, 2000; Vivian, 2006; Kramer et al., 2010; Hauke et al., 2011; Boelk and Kramer, 2012; Shin et al., 2016; Longacre et al., 2018; Benson et al., 2019; Hansen and Tjørnhøj-Thomsen, 2020). The concept of conflict can be analyzed both from a psychological and bioethical perspectives, depending on whether the conflict presents a psychological or ethical connotation. Current bioethical literature on the topic, has shown that “moral conflict” between parties may originate because of different factors. A first source of “moral conflict” lies in the so called “ethical disagreement”, namely the fact that the patient and the caregiver have different (and in some cases incompatible) values with respect to care decisions and treatment goals (Hauke et al., 2011; Kramer and Yonker, 2011; Korfage et al., 2013; Benson et al., 2019; Laryionava et al., 2021). In other cases, “moral conflict” arises when the patient or caregiver base their decisions on personal interests, creating what we referred to as “conflict of interest” (Levine and Zuckerman, 1999, 2000; Blackler, 2016; Laryionava et al., 2018). Other authors reveal that “moral conflict” can be related to the concept of agency. Indeed, during the oncological care path, patients and caregivers are *autonomous agents* that should make medical decisions. Conflicts may arise in this case when patients and/or caregivers feel a compromising of their autonomy, experiencing moral distress. Caregivers may unintentionally manipulate patients, compromising their autonomy, or viceversa, patients may oblige caregivers to decide in place of them, transferring their autonomy (Vivian, 2006; Blackler, 2016; Osamor and Grady, 2018; Benson et al., 2019). Finally, moral conflict may be the consequence of purely relational and experiential aspects. This last kind of moral conflict originates from a non-recognition of the other as “ontologically different” from the subject primarily asked to take the decision. Sometimes, cancer patients don't feel recognized in their ontological individuality by their caregivers, even though they appreciate their support (Kagawa-Singer and Wellisch, 2003; Hansen and Tjørnhøj-Thomsen, 2020).

Drawing upon these premises, a parallel empirical bioethics study will be conducted, with the aim to further explore the concept of moral conflict, investigating it in a qualitative manner. Differently from most of the bioethics literature which focuses on late cancer, i.e., when the patient is proxy to death, our study aims to investigate this phenomenon at the beginning of cancer trajectory, when potential moral conflicts may impact throughout the entire therapeutic process (Davies et al., 2015). A group of 20–25 dyads already enrolled for the main study will be invited to reply to in-depth qualitative face-to-face semi-structured interviews aimed at identifying and mapping possible decision-making conflicts of a moral nature, namely “moral conflict”, arising in the patient-caregiver relationship and potentially affecting the care process. After a very brief explanation of what an ethical issue is and to what extent it differentiates from, e.g., psychological issues, dyads will be asked whether they have already experienced some sort of moral conflict, to describe its nature, and to report whether and how this conflict impacted on their relationship, medical decisions, and adherence to cure. Furthermore, it will be investigated whether dyads would consider useful/beneficial to be offered for free a support service dedicated to the discussion and management of moral conflicts occurring within the patient-caregiver relationship and potentially affecting the oncological care process.

### Participants

Patients who had access to the Division of Breast Surgery and to the Division of Urologic Cancer Surgery at the European Institute of Oncology (IEO), with a suspected cancer or a newly cancer diagnosis and accompanied by a caregiver, will be reported by the oncology and nursing team. Then, the researcher will contact the reported patients though a phone call and/or an email. During the first contact, one researcher of the team informs patients about the study purposes and the procedure. Then, patients are asked to share the information with a caregiver (the definition of caregiver will be provided so that the patient can consciously decide about their main caregiver) and to invite him/her to join the study. An official invitation letter, the informed consent, and the link to the online survey (*via* Qualtrics™ Platform), will be then sent by email to the enrolled patients and referred caregivers. Time schedule of recruitment, interventions, assessment, and follow-ups are available in the flow diagram (see Table 1).

**Table 1 T1:** Schedule of enrolment, intervention, and assessment.

	**Enrolment**	**Allocation**	**Post-allocation**	**Close-out**
Timepoint		T0	T1	T2
**Enrolment**				
Eligibility screen	X			
Informed consent	X			
Allocation		X		
**Intervention**				
Psychological support consultation		X	X	X
Control group		X	X	X
**Assessment**				
Sociodemographic data		X		
CPS		X	X	
Decisional role			X	X
PAIR-communication subscale		X		X
MBSS		X		
HADS		X	X	X
MSPSS		X	X	X
SF-12		X	X	X
SDM-Q-9		X	X	
CARE		X	X	
SWD			X	X
ADQ				X

### Eligibility criteria

Tables 2, 3 show inclusion and exclusion criteria for newly diagnosed breast and prostate cancer patients and for the caregivers. Regarding caregivers, we have decided to include any person that the patients considered important to them and that they felt by their side in this difficult period.

**Table 2 T2:** Inclusion and exclusion criteria for patients.

**Inclusion criteria**	**Exclusion criteria**
Patients with a newly breast or prostate cancer diagnosis that currently are within the diagnostic assessment process and have to discuss their treatment with the oncologists.	Presence of early mental disorders (before age 40) or severe neurological disorder.
Early-stage cancer (I or II)	Patients with advanced stage cancer for which the path is already defined (palliative care patients).
Age ≥ 18	
Able to give informed consent^a^	
Able to read, speak, and understand Italian^a^	

a This criterion was not present in the study protocol approved by the Ethical Committee.

**Table 3 T3:** Inclusion and exclusion criteria for caregivers.

**Inclusion criteria**	**Exclusion criteria**
Taking care of the patient	Presence of early mental disorders (before age 40) or severe neurological disorders
Age ≥ 18	
Able to give informed consent^a^	
Able to read, speak, and understand Italian^a^	

a This criterion was not present in the study protocol approved by the Ethical Committee.

### Sample size and power calculation

One hundred two dyads are needed for this study considering 51 male patients enrolled in the Division of Urologic Cancer Surgery and 51 female patients enrolled in the Division of Breast Surgery at IEO in Milan.

The variable “compliance with therapy” measured by ADQ (DiMatteo et al., 1993), including the subscales Interpersonal Aspects of Care (range: from 8 to 40) and Subjective Norms (range: from −18 to 18), was used as the primary outcome of interest in the sample size calculation. The hypothesis is that the involvement of caregivers increases the patient's adherence to treatment recommendations, which in turn directly impacts the patients' prognosis as widely demonstrated in the literature (Ricci-Cabello et al., 2020). The sample size calculation was based upon the assumption that we will observe a difference of 3 points in the average values of the two subscales IAC and SN, in favor of the intervention group. A standard deviation of ~5 points is assumed for both subscales (untransformed values) according to data presented by DiMatteo et al. (1993), leading to a hypothesized effect size of 0.6. This effect size should be considered as a medium-large effect according to Cohen (2013), and it is considered to provide clinical relevance. A two-sample *t*-test will be used to compare the mean subscale values in the intervention group vs. control group. With a 1:1 randomization ratio, a total of 88 patients (44 in the intervention group and the 44 in the control group) are required to provide 80% power to detect a difference ≥ 3 points, with a type I error of 5% (two-sided *t*-test). Assuming a drop-out rate at 6-months of ~15%, a total of 102 patients will be required.

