### Study design and setting

This study will be conducted at the European Institute of Oncology of Milan (Italy). The IEO is a specialized Hospital and internationally recognized Cancer Center located in Italy working on research, prevention, diagnosis, and treatment of cancer. The IEO offers to the patients innovative and personalized care, from the diagnosis onward. Study design is longitudinal randomized, with a 1:1 allocation ration analyzing the proposed primary and secondary aims.

Participants will be randomly assigned to one of the two following arms: (1) dyads receiving a psychological support consultation (experimental group); (2) dyads receiving no psychological support consultation (control group). For ethical reasons, the dyads in the control group will be offered the option to receive the psychological support consultation at the end of the study, but only in case the psychological support consultation turns out to be beneficial for the dyads. Indeed, the study did not foresee a cross sectional design.

The dyads assigned to the experimental group will be contacted by the clinical psychologist to schedule an appointment for the psychological support consultation. The consultation will be performed within the period of diagnostic assessment, preferably within the date of pre-hospitalization for surgery or for starting other cancer treatments. The consultation will be carried out by a clinical psychologist with a master's degree in clinical psychology, a state certificate exam, and previous internship in psychological support intervention for cancer patients.

The consultation will last 60 min and will include the following steps and areas of focus:

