**Figure 1 F1:**
[figure not shown]
Study protocol flowchart.

The assignment to one of the two arms will not be disclosed to the participants and to the experimenters who will interface with the subjects for consultation and psychological assessment through questionnaires. Only personnel who analyze the data collected from the study will be aware of participants who receive psychological support consultation. Participants will be randomized during T0 assessment, immediately after the collection of socio-demographic and clinical data and psychological measures.

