### Data analyses

Missing data: presence of missing data will be checked before conducting the main analyses. If a subject does not complete T1 and T2 he/she will be excluded from the analysis.

Normal distribution of continuous variables will be assessed (using skewness and kurtosis) before conducting the main analyses. Non-normal distribution will be handled by applying either non-parametric tests or SEM with an estimator for non-normal distribution.

Statistical analyses will be performed in SPSS version 25. Socio-demographic data collected in this study will be described in terms of mean, standard deviation, median, minimum, and maximum or reported frequencies in combination with confidence intervals. The preliminary analysis will be carried out through the Pearson or Spearman correlations r between the variables considered and by exploratory analysis of variance. To compare the two experimental and control groups, the *t*-tests (in case of normal distribution) or Mann-Whitney U tests (in case of non-existence of a normal distribution) will be applied, or cross tables with the chi-squared tests and (if necessary) the generalized exact Fisher's tests.

The main analysis will consist of an evaluation at different time-points of the psychometric scales, using linear models with mixed effects for repeated measures. The scales of interest will constitute the dependent variable, whereas the independent fixed factors will be the time of visit, the intervention group, the scale measured at baseline and the interaction term between the time of the visit and the intervention and, as a random effect, the patient. Multiple linear regressions will be calculated for both groups to evaluate the weight of each variable on the main outcome.

The semi-structured interviews will be analyzed by NVivo v10, a qualitative data analysis software.

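### Cancer site is built into the sample by a 51/51 quota but left out of the ADQ t-test and the mixed models, which forgoes some precision

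*Protocol article*

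**What the plan says.** **Sample.** The section Sample size and power calculation reaches 102 dyads "considering 51 male patients enrolled in the Division of Urologic Cancer Surgery and 51 female patients enrolled in the Division of Breast Surgery". The split by cancer site is thus set in advance, and site coincides with sex and with hospital division.

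**Sizing test.** The same section assumes "we will observe a difference of 3 points in the average values of the two subscales IAC and SN", with an SD of about 5 points on each. It states that a two-sample t-test "will be used to compare the mean subscale values in the intervention group vs. control group". No covariate is named.

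**Main model.** Under Data analyses, "the independent fixed factors will be the time of visit, the intervention group, the scale measured at baseline and the interaction term" of visit time with intervention, and "as a random effect, the patient". Site, division and sex are not among these terms. The same section also plans multiple linear regressions for both groups, to weigh the variables against the main outcome. These are not described as an arm comparison adjusted for site.

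**Timing of ADQ.** The T2 measures section and Table 1 place ADQ at T2 only.

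**Allocation.** Study design and setting says "Study design is longitudinal randomized, with a 1:1 allocation ration". The text after the Figure 1 caption adds "Participants will be randomized during T0 assessment, immediately after the collection of socio-demographic and clinical data and psychological measures". Nothing is said about stratification, blocking or simple randomisation.

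**The concern.** The trial recruits equal numbers from two populations that differ in sex, disease and treating division. One of the two sizing subscales, Interpersonal Aspects of Care, may well reflect the treating team, and the teams differ between divisions. If mean ADQ scores differ by site, that difference stays in the error term of an unadjusted comparison.

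For scales with a T0 score (HADS, MSPSS, SF-12, SDM-Q-9, CARE), the baseline covariate would take up part of any stable site difference. ADQ has no such score, so the outcome that sizes the trial is the one left without adjustment.

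What is at stake is power on a design with little to spare. The site of every patient is known before randomisation, so the information is free.

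**Working it through.** **Inputs from the article:** difference 3 points, SD about 5, two-sided alpha 0.05, power 80%, 44 per arm (88), drop-out about 15%, total 102, site split 51/51. **Assumed, because the article gives no figure:** the site gap in mean ADQ, taken as 0.3, 0.5 and 0.8 SD.

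**1. The plan's own figure.**
- Effect size = 3/5 = 0.6.
- Normal approximation: n per arm = 2 × (1.960 + 0.842)² / 0.6² = 43.6, so 44 per arm and 88 in total. The stated figure reproduces.
- Exact noncentral t: power is 79.5% at 44 per arm and 80.4% at 45. The difference is trivial.
- Drop-out: 88 × 1.15 gives 102, whereas 88/0.85 gives 104. The two are close.
- Expected completers: 102 × 0.85 = 86.7, so about 43 per arm. Exact unadjusted power at 43 per arm is 78.5%.

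**2. What a site term would recover.** With a 50:50 site mix and a gap of g SDs, site explains R² of the variance:
- R² = (g/2)² if g is in units of the total SD.
- R² = (g²/4)/(1 + g²/4) if g is in units of the within-site SD.

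The effect size with site in the model is 0.6/√(1 − R²). Power is taken from the noncentral t with 43 per arm and 83 degrees of freedom (84 less one).

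| Assumed site gap | R² | Effect size | Power with site term |
|---|---|---|---|
| none | 0 | 0.600 | 78.5% |
| 0.3 SD (1.5 points) | 0.022 | 0.607 | 79.4% |
| 0.5 SD (2.5 points) | 0.059-0.063 | 0.619-0.620 | 81% |
| 0.8 SD (4 points) | 0.138-0.160 | 0.646-0.655 | 84-85% |

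The ranges within a row come from the two definitions of the gap. With no gap, the lost degree of freedom costs about 0.01 percentage points.

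**3. Type I error of the unadjusted t-test.** Simulated with 44 per arm, total SD 5 and 20,000 runs per setting.

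| Site gap | Unstratified allocation | Stratified by site |
|---|---|---|
| 0 | 5.0% | 4.8% |
| 2.5 points | 5.0% | 4.1% |
| 5 points | 5.0% | 2.5% |

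No setting gives an excess of false positives. Under stratified allocation the unadjusted test is conservative.

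**4. Chance imbalance, only if allocation is unstratified.** With 51 per arm, the number of prostate dyads in one arm is hypergeometric(102, 51, 51).
- P(arms differ by 9 or more prostate dyads) = 11.3%.
- P(differ by 11 or more) = 4.7%.
- A split of 11 is 11/51 = 22 percentage points. With a 2.5-point site gap it moves the unadjusted difference by 0.216 × 2.5 = 0.54 points.
- The standard error of the comparison at 43 per arm is 5 × √(2/43) = 1.08 points, so that shift is about half a standard error.

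**The case against.** The strongest reply is that leaving a prognostic covariate out of a randomised comparison of means is legitimate and unbiased. The assumed SD of 5 can be read as a total SD, in which case site variance is already inside the power calculation. The gain from adjustment rests on a site gap that the article does not give; at 0.3 SD it is about one percentage point, and with no gap it is nil. For scales with a T0 score, baseline adjustment already does part of the work. All of this stands, and it limits the point to one of efficiency.

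A reader might infer two stronger claims that the article does not support:

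- **That randomisation is plain, unstratified 1:1.** The article gives the ratio and the timing only. A condensed article commonly leaves the scheme to the full protocol, and the footnotes to Tables 2 and 3 show that a separate ethics-approved protocol exists. A 51/51 quota fits separate lists per division as well as it fits a single list.
- **That an unlucky split by site would bias the result.** Under unstratified allocation, a shift such as 0.54 points is chance deviation that the unadjusted test's error rate already covers, as the simulated 5.0% shows.

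The reply does not remove the omission itself. The article names its model terms and its sizing test, and both leave out the factor on which the sample is built. For ADQ, no baseline score makes up for it.

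**Conclusion.** The point holds as a low-cost improvement in precision. It does not invalidate the stated sample size and shows no inflation of type I error. At 43 per arm, a site term would lift power from 78.5% by about 1 percentage point at a gap of 0.3 SD, 2.5 points at 0.5 SD and 6 points at 0.8 SD. At 0.5 SD, that is enough to bring the comparison back above 80%. These gains rest on an assumed site gap, on a 50:50 site mix among completers, and on the article's own difference of 3 and SD of 5. The case for the term does not depend on the randomisation scheme. If allocation is unstratified, the term removes the effect of any chance imbalance by site. If allocation is stratified by division, it restores the nominal error rate of an otherwise conservative test.

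**What to change.** Before the arms are compared:

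- Replace the plain two-sample t-test on each ADQ subscale with a linear model containing arm and cancer site (division).
- Add cancer site as a fixed factor to the mixed models. This matters most for measures without a T0 score, such as the Satisfaction with Decision scale.
- State whether allocation is stratified by division, so that the reader can see that analysis and design agree.

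The cost is one degree of freedom per model and no new data. The term must be specified in advance, because adding it once results are known would be a post hoc choice.

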## Methods and analysis

### Study aims

The *primary aim* of the present study is to assess whether a psychological support intervention for newly diagnosed breast and prostate cancer patients-caregivers' dyads may promote their synergy in the TDM process and may improve the compliance/adherence to treatment and the satisfaction with the (shared) medical decisions through a randomized study.

The *secondary aim* are: (a) to assess the preferences and degree of agreement between newly diagnosed breast and prostate cancer patient and caregiver on the latter's involvement in the TDM process; (b) to investigate which factors and dynamics contribute to a collaborative relationship between newly diagnosed breast and prostate cancer patient and caregiver, and determine the level of involvement of the caregiver; (c) to understand what are the effects that the involvement of caregivers have on newly diagnosed breast and prostate cancer patients in terms of patients' perceived social support, satisfaction with the clinical path, compliance with therapy, quality of life, anxiety and depression, and perceived empathic relation with clinicians.

Finally, since the issue of caregiver's involvement has been also investigated within the bioethical literature and presents bioethical connotations as well, the ethical issues surrounding this dyadic relationship will be also explored. Accordingly, in parallel with the main study, a secondary investigation exploring the presence and nature of ethical disagreements within family relationships, in the context of diagnosis of and treatment to cancer will be carried out.

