### T2 measures

#### Adherence to therapies

The Adherence Determinants Questionnaire [ADQ (DiMatteo et al., 1993)] is a multifactorial tool aiming at evaluating the elements of patients' self-adherence to cancer treatments, taking into consideration a set of cognitive and motivational skills, as well as social and behavioral variables. Response options for each item comprise 5-point Likert scales (1 = *strongly disagree;* 2 = *disagree;* 3 = *neither agree nor disagree;* 4 = *agree; 5* = *strongly agree*). Seven subscales are considered: Interpersonal Aspects of Care; Perceived Utility (Benefits/Costs and Efficacy); Perceived Severity; Perceived Susceptibility; Subjective Norms; Intentions; Support/Barriers. The components of the ADQ were found to be generally reliable (median alpha reliability = 0.76) (DiMatteo et al., 1993).

In addition, the following questionnaires will be re-administered: item from Shin and colleagues (Shin et al., 2017) for Decisional Role; 5 items from PAIR (Schaefer and Olson, 1981) (dyadic communication); The HADS (Zigmond and Snaith, 1983); The MSPSS (Zimet et al., 1988); The SF-12 Health Survey (Ware et al., 1996); The SWD (Holmes-Rovner et al., 1996).

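### The primary outcome is labelled compliance with therapy, but the two ADQ subscales tested score determinants of adherence, so a difference on them cannot by itself show better treatment adherence

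*Protocol article*

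**What the plan says.** Under Sample size and power calculation, the protocol article names the outcome on which the trial is sized: "The variable “compliance with therapy” measured by ADQ". The same sentence specifies two subscales and makes them the primary endpoint of the calculation. The hypothesis follows: "The hypothesis is that the involvement of caregivers increases the patient's adherence to treatment recommendations". It adds, with a citation, that adherence bears on prognosis. The planned difference is 3 points on each subscale with an SD of about 5, tested by a two-sample t-test.

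The T2 measures section, under Adherence to therapies, introduces the instrument as "The Adherence Determinants Questionnaire" and describes its purpose as "evaluating the elements of patients' self-adherence to cancer treatments, taking into consideration a set of cognitive and motivational skills", along with social and behavioural variables. It lists seven subscales: Interpersonal Aspects of Care, Perceived Utility, and then "Perceived Severity; Perceived Susceptibility; Subjective Norms; Intentions; Support/Barriers".

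Study aims makes adherence part of the primary aim: the intervention "may improve the compliance/adherence to treatment and the satisfaction with the (shared) medical decisions". Hypothesis (b) at the end of the Introduction likewise predicts better treatment adherence after the consultation.

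**The concern.** The label and hypothesis speak of adherence, meaning whether patients follow their treatment. The scores under test come from a questionnaire whose own title says that it measures what determines adherence. By name, one chosen subscale concerns the interpersonal side of care and the other perceived norms.

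The consultation, as described under Study design and setting, deals with the dyad's mutual support and with how they see their relationship with the medical team. That content is close to what the two subscales name, so it is plausible, though not shown, that the scores could move without any change in treatment taking.

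If the plan is followed as worded, a difference on these scores would be reported as better compliance. That is a stronger statement than the data can carry, and it would be made on the primary outcome.

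**Working it through.** **1. The plan's own figure.** Inputs, all from Sample size and power calculation: difference 3, SD 5, two-sided alpha 5%, power 80%, 1:1 allocation, drop-out about 15%.

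- Effect size: 3 / 5 = 0.6, as stated.
- Per arm, normal approximation: n = 2 × (1.960 + 0.842)² × (5/3)² = 2 × 7.85 × 2.78 = 43.6, rounded up to 44. Total 88, as stated. Power at 44 per arm is 80.4% by this formula and 79.5% by the exact t-test.
- Drop-out: 88 × 1.15 = 101.2, rounded up to 102, as stated. Dividing instead, 88 / 0.85 = 103.5, gives 104, a difference of two patients that does not bear on this point.

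The calculation reproduces. Every input refers to a score on Interpersonal Aspects of Care or Subjective Norms. None refers to treatment taken.

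**2. Label against measure.**

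| Place in the protocol article | What it refers to |
|---|---|
| Sample size, outcome label | Compliance with therapy |
| Sample size, hypothesis | Increased adherence |
| Sample size, difference, SD and test | Two ADQ subscale scores |
| T2 measures, title of the instrument | Determinants of adherence |
| T2 measures, seven subscales | None named as adherence behaviour |

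**3. Does another measure fill the gap?** Table 1 lists sociodemographic data, CPS, decisional role, PAIR, MBSS, HADS, MSPSS, SF-12, SDM-Q-9, CARE, SWD and ADQ. ADQ is the only entry concerned with adherence, and it appears at T2 only. No row records doses taken, attendance or treatment records. The Empirical bioethics study will ask 20–25 dyads, among other things, whether moral conflict affected adherence. Those data are qualitative, come from a subset, and are not planned as a comparison of the randomised arms.

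**4. Could an analysis plan settle it?** The article states which instruments are given and when. An analysis plan can choose among the data collected but cannot supply a measure that is not scheduled.

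**5. Consequence.** The randomised comparison can show an effect of the consultation on two determinant scores. Moving from there to adherence needs a link between score and behaviour. The documents give no figure for that link and the schedule collects nothing to estimate it.

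**The case against.** The strongest reply is that a self-report determinants scale is a legitimate and common choice, and that the article hides nothing: it gives the instrument's full title and all seven subscales. Its description of the tool speaks of self-adherence and ends with behavioural content: "taking into consideration a set of cognitive and motivational skills, as well as social and behavioral variables". The items are not reproduced, so what the two subscales capture is inferred from their names. All of this stands, and it supports relevance to adherence. It does not turn either subscale into a record of adherence, and the remedy keeps the outcome as it is.

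A second reply is that the word introducing the two subscales could be non-exhaustive. The difference, SD and test are nevertheless given for these two alone, and no other listed subscale is named as behaviour, so the point holds on either reading.

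A reader might infer more than the documents support:

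- *That the trial is underpowered for adherence.* This would need a correlation between subscale and behaviour, and the assumption that the whole effect passes through the subscale. The documents give neither. The stated power is claimed only for a 3-point subscale difference, and for that it is sound.
- *That the plan commits to claiming a prognostic benefit.* The prognosis clause is cited rationale. Study aims is worded as what the intervention may do, and the closing remarks of the Discussion are hedged. No rule turns a subscale difference into a claim about prognosis.
- *That the trial tests the wrong cause, because the hypothesis sentence in the sample size section speaks of caregiver involvement.* The Introduction's hypotheses and Study aims both name the consultation or intervention. One loose sentence does not change the comparison.
- *That no information on adherence is gathered at all.* The interviews touch on it, though not in a form that could support a comparison between arms.

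**Conclusion.** The point holds as a mismatch between the label and hypothesis on one side and the measured outcome on the other. A difference on Interpersonal Aspects of Care or Subjective Norms at T2 would support a statement about determinants of adherence as scored by ADQ. It would not by itself support the statement that the consultation improves treatment adherence.

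The size is qualitative: it limits what may be concluded from the primary outcome and leaves 44 per arm, 88 and 102 unchanged. The conclusion rests on the instrument's title and description, the names of its subscales, and the absence of any quantitative measure of treatment taken from Table 1. It needs no assumption about how strongly the scores track behaviour.

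**What to change.** In Sample size and power calculation:

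- Name the primary outcome ADQ adherence-determinant scores (Interpersonal Aspects of Care, Subjective Norms) at T2.
- State the hypothesis as the effect of the consultation on these scores.
- Add that conclusions will be limited to adherence determinants and will not extend to adherence or prognosis.

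Where the Introduction's aims and hypothesis (b), and Study aims, speak of improving adherence, refer to adherence determinants as measured by ADQ. Leave the other aims there (agreement, synergy, satisfaction, distress) as they are.

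The remaining ADQ subscales, Intentions among them, are already collected at T2 and can be reported as supportive. The documents give no basis for ranking one of them as nearest to behaviour.

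The change needs no new data, visits or participants and does not alter the sample size. Its cost is a more modest claim.
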